### Power and Sample Size for the Primary Outcome

The trial is powered for the primary outcome, MDS UPDRS-IV total score. A differential effect size of *d* = 0.89 in the change of OFF-time for PDAE vs. walking using data collected by Uc et al. (30) was observed (Table 1) (30).

Given the study design's 3- and 16-month timepoints, we will use Holm's procedure (62) to control for multiple testing. The alpha levels will be 0.025 and 0.05 for *p*-values in ascending order for comparing PDAE and WALK in the changes from the baseline at 3 and 16 months. The observed effect size (*d* = 0.89) is from participants that finished their programs in the shorter duration pilot studies; therefore, we expect the intent-to-treat effect size will be reduced. Thus, we power the study for an attenuated effect of the observed effect: *d* = 0.7, which is 64% of the observed effect size in our pilot study or 79% of the estimated effect vs. walking, giving us 81 and 88% power for the comparisons at alpha level of 0.025 and 0.05, respectively. With a sample size of *n* = 41 completers per group, total *n* = 82, we additionally expect to have medium to high (60–80%) power to detect differences between the PDAE and WALK groups on the visuospatial outcome (Aim 2), given that the estimated effect size for Corsi Blocks is 0.76 vs. a cognitively engaging contact control (63). We will assume 25% attrition and will therefore recruit 102 participants with PD. For the exploratory variables, we will only focus on effect estimation instead of inference testing given that we do not know the effect size.

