**Figure 2 F2:**
[figure not shown]
Activation patterns Post-PDAE. Increased activation was noted in left inferior frontal gyrus area 45 **(A)** and inferior temporal gyrus area 20 **(B)** at post compared to baseline after 12 weeks of PDAE.

Our central hypothesis is that PDAE is a cognitively and socially engaging, potentially neuroprotective AE, which reduces OFF-time and improves spatial cognition in PD superior to walking aerobic exercise (WALK). Our goals are to identify whether 16 months of PDAE training (partnered, complex, skilled multirhythmic, and cognitively engaging walking activities) is superior to a WALK program for reducing OFF-time, improving cognition, and slowing neurodegeneration in PD. The WALK control group controls for AE and basic walking practice to isolate the cognitive aspects required to perform skills learned in PDAE.

Here, we describe the design and rationale of a clinical trial to determine whether PDAE is more effective than WALK at addressing OFF-time in people with mild–moderate PD. The PAIRED trial will (1) investigate PDAE's relationship with OFF-time and patient-reported drug efficacy, a patient-centered outcome that has received little attention in the context of exercise studies, over short (3 months) and long terms (13 month); (2) determine whether PDAE is a robust model for simultaneously delivering cognitive, motor skill, and AE training; (3) use novel imaging techniques to evaluate rates of neurodegeneration in the SNc of PD patients after long-term exercise intervention; and (4) investigate the efficacy of a novel, long-term 13-month maintenance phase of PDAE, which may have great utility for patients if less intense maintenance periods are shown to be effective after an initial more intensive training bout. We hypothesize that PDAE will improve OFF-time superior to WALK at a 3- and 16-month follow-up, that PDAE will improve spatial cognition superior to WALK, at 3- and at 16-month follow-up, and that we will note slowed SNc NM loss and decreased iron accumulation rate in PDAE vs. WALK.

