### Analyses

#### Aim 1

We will analyze the primary study outcome with a mixed effect model (treating subject as random) with between-subjects effect of group (PDAE vs. WALK) and within-subjects timepoints (study entry, 3-month follow-up, 16-month follow-up) plus their interaction term. If the interaction term is significant, we will test differences between PDAE and WALK in the change from baseline to 3 months and from baseline to 16 months using Holm's procedure to control for multiple testing. We will consider covariates sex and H&Y staging (<III, ≥III) in the analyses.

#### Aim 2

The secondary outcome Corsi Blocks Score will be analyzed using a similar mixed effects model.

#### Aim 3

We will use similar analyses. We will use mixed effects model except that it will be a two-group (PDAE vs. WALK) and a two-level variable for time (study entry vs. 16-month follow-up).

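### The 81% and 88% are powers of single t-tests at a fixed alpha, but they are attached to the ordered p-values of a Holm procedure, for which they do not hold

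*Protocol article*

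**What the plan says.** In Power and Sample Size for the Primary Outcome, the protocol adopts Holm's procedure for the two follow-up times (months 3 and 16) and assigns the levels by rank: "The alpha levels will be 0.025 and 0.05 for *p*-values in ascending order for comparing PDAE and WALK in the changes from the baseline". It takes an attenuated effect of d = 0.7 and concludes that this is "giving us 81 and 88% power for the comparisons at alpha level of 0.025 and 0.05, respectively". The sample is given in the next sentence: "With a sample size of *n* = 41 completers per group, total *n* = 82".

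Analyses, Aim 1 confirms that the contrasts are tested "from baseline to 3 months and from baseline to 16 months using Holm's procedure to control for multiple testing", and only if the group-by-time interaction is significant. The hypothesis at the end of the Introduction is: "We hypothesize that PDAE will improve OFF-time superior to WALK at a 3- and 16-month follow-up".

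The section gives no correlation between the 3- and 16-month changes, does not state sidedness, and gives no power for the step-down procedure as a whole.

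**The concern.** Under Holm no time point has a pre-assigned alpha. The comparison at 0.025 is whichever has the smaller p-value. The comparison at 0.05 is the other one, and it can be declared significant only if the smaller p-value has already passed 0.025. The power of the first step is therefore the chance that at least one time point succeeds, and the power of the second is the chance that both do. A stand-alone t-test at 0.025 or 0.05 measures neither.

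Because the protocol defines the two levels by p-value rank and then attaches 81% and 88% to them, a reader will take 88% as the power of the second step. That matters for the claim of benefit at both 3 and 16 months, where the printed figure is too favourable. For success at one time point or more, the printed 81% is too pessimistic.

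**Working it through.** **Inputs.** From the sample-size section: d = 0.7, 41 completers per group, 1:1, Holm with levels 0.025 and 0.05. Assumptions: d = 0.7 at both time points (the protocol gives one d without naming a time) and a correlation r between the two change scores, varied because it is not given.

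**Step 1: reproduce the printed figures.** Two-sample t-test, two-sided, 80 degrees of freedom, noncentrality 0.7 × √(41/2) = 3.17:
- alpha 0.025: 81.0%
- alpha 0.05: 87.9%

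These are the printed 81% and 88%. One-sided tests would give 87.9% and 93.3%, so the pair is two-sided.

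**Step 2: Holm by hand at the two extremes.** Write a = 0.810 and b = 0.879.

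At r = 0:
- at least one: 1 − (1 − a)² = 1 − 0.190² = 96.4%
- both: b² − (b − a)² = 0.7726 − 0.0048 = 76.8%. The subtracted term is the case where both p-values lie between 0.025 and 0.05, so Holm rejects neither.
- a given time point: a + (b − a) × a = 0.810 + 0.069 × 0.810 = 86.6%

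At r = 1 the two p-values coincide, and all three quantities equal a = 81.0%.

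**Step 3: Holm in between.** Simulation of the two t-statistics (1,000,000 trials per setting). At least one = P(min p ≤ 0.025). Both = P(min p ≤ 0.025 and max p ≤ 0.05).

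| r | At least one | A given time point | Both | Both, given at least one |
|---|---|---|---|---|
| 0 | 96.4% | 86.6% | 76.8% | 79.7% |
| 0.3 | 94.0% | 86.0% | 78.1% | 83.1% |
| 0.5 | 91.9% | 85.6% | 79.2% | 86.2% |
| 0.6 | 90.8% | 85.4% | 79.9% | 88.0% |
| 0.7 | 89.5% | 85.1% | 80.7% | 90.2% |
| 0.8 | 88.0% | 84.8% | 81.6% | 92.8% |
| 0.9 | 85.9% | 84.3% | 82.6% | 96.1% |
| 0.95 | 84.5% | 83.8% | 83.0% | 98.3% |
| 1 | 81.0% | 81.0% | 81.0% | 100% |

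The power for both does not reach 88% at any correlation run. Over r = 0 to 0.95 it is 5 to 11 points below the printed figure (88 − 83.0 = 5.0; 88 − 76.8 = 11.2). The power for at least one is 3.5 to 15.4 points above the printed 81%.

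**Step 4: the interaction gate.** With three visits and two groups the interaction has two degrees of freedom. Its level is not stated; I take 0.05. Modelled as a Hotelling T² test on the two changes that must be significant first, the power for both is about 77–80% over r = 0 to 0.95. The power for at least one runs from about 96% at r = 0 down to about 80–81% at r = 0.95, the last point depending on the reference distribution used for the gate.

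**The case against.** **The arithmetic is right.** This stands. Each figure is exact for a single comparison at the stated alpha, and the fault lies only in attaching them to ordered p-values.

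**The pair can be read as a bracket.** Under Holm a given time point is effectively judged at 0.025 or 0.05, depending on the other result, so its power lies between 81% and 88%, and it does (84–87%). That would be useful information, but the protocol does not present the figures as bounds. It presents them as the powers at two levels that it has just tied to p-value rank.

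**The 88% could be power for the second step once the first has been passed.** That conditional value runs from about 80% to 100% and equals 88% only near r = 0.6. The protocol states neither the condition nor a correlation, and its 88% is the unconditional t-test value.

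**Low correlations are implausible.** This has force. Both changes share a baseline, and a random-intercept model implies r = 0.5 (covariance σ² over variance 2σ²). From there to r = 0.95 the power for both is 79–83%, so the gap is 5 to 9 points rather than 11. The direction is unchanged.

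**Success at both time points is not required.** Also correct. A reader might infer from the hypothesis that the trial succeeds only if both contrasts are significant, and hence that it is underpowered. The protocol sets no such rule, and Holm allows either time point to be claimed alone.

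**A condensed article may leave step-down power to the full protocol.** It may omit that detail. Here, however, it prints figures that do not match the procedure it defines.

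**Conclusion.** The point holds as a mislabelled power statement, with errors in both directions. With d = 0.7 at both times, 41 per group, two-sided tests and r from 0 to 0.95, Holm gives about 85–96% for at least one time point, about 84–87% for a given time point and about 77–83% for both. The printed 81% understates the first step, and the printed 88% overstates the step tested at 0.05. That second conclusion does not depend on the unstated correlation.

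The documents do not support reading this as a calculation error or as a sample size that is too small. Power for at least one time point and for a given time point exceeds 81% across that range, and power for both is near 80%. These figures accept 41 completers per group as planned, and they are before the interaction gate, which can only lower them.

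**What to change.** Keep N and Holm, and rewrite the power sentence in one of two ways:

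1. Report the Holm powers at d = 0.7 and 41 per group for at least one, a given, and both time points, with the assumed correlation between the two changes. At r = 0.5, for example, these are about 92%, 86% and 79%.
2. Keep 81% and 88%, but describe them as powers of a single two-sided t-test at fixed alpha 0.025 and 0.05, and state that they are not the powers of the Holm steps.

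If the interaction test stays as a gate, say whether the Holm figures are before it or include it, and at what level the gate is tested.

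The cost is a sentence or two, with no change to sample size, test or conduct. The downside is a less favourable figure for claiming benefit at both time points.

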## Abstract

Parkinson's disease (PD), an intractable condition impairing motor and cognitive function, is imperfectly treated by drugs and surgery. Two priority issues for many people with PD are OFF-time and cognitive impairment. Even under best medical management, three-fourths of people with PD experience “OFF-time” related to medication-related motor fluctuations, which severely impacts both quality of life and cognition. Cognitive deficits are found even in newly diagnosed people with PD and are often intractable. Our data suggest that partnered dance aerobic exercise (PDAE) reduces OFF-time on the Movement Disorders Society Unified Parkinson Disease Rating Scale-IV (MDS-UPDRS-IV) and ameliorates other disease features, which motivate the PAIRED trial. PDAE provides AE during an improvisational, cognitively engaging rehabilitative physical activity. Although exercise benefits motor and cognitive symptoms and may be neuroprotective for PD, studies using robust biomarkers of neuroprotection in humans are rare. We propose to perform a randomized, controlled trial in individuals with diagnosed mild–moderate PD to compare the efficacy of PDAE vs. walking aerobic exercise (WALK) for OFF-time, cognition, and neuroprotection. We will assess neuroprotection with neuromelanin-sensitive MRI (NM-MRI) and iron-sensitive (R2^*^) MRI sequences to quantify neuromelanin loss and iron accumulation in substantia nigra pars compacta (SNc). We will use these biomarkers, neuromelanin loss, and iron accumulation, as tools to chart the course of neurodegeneration in patients with PD who have undergone long-term (16 months) intervention. We will randomly assign 102 individuals with mild–moderate PD to 16 months of PDAE or WALK. The 16-month intervention period will consist of Training (3 months of biweekly sessions) and Maintenance (13 months of weekly sessions) phases. We will assess participants at baseline, 3 months (immediately post-Training), and 16 months (immediately post-Maintenance) for OFF-time and behaviorally and physiologically measured cognition. We will acquire NM-MRI and R2^*^ imaging data at baseline and 16 months to assess neuroprotection. We will (1) examine effects of Training and Maintenance phases of PDAE vs. WALK on OFF-time, (2) compare PDAE vs. WALK at 3 and 16 months on behavioral and functional MRI (fMRI) measures of spatial cognition, and (3) compare PDAE vs. WALK for effects on rates of neurodegeneration.

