## Study Design

### Overall Study Design

The PAIRED trial builds upon more than 10 years of research investigating unique motor, cognitive, and symptomatic benefits of PDAE. The study will perform a two arm, randomized controlled trial comparing efficacy of PDAE vs. WALK for improving OFF-time and visuospatial cognition among individuals with PD who report OFF-time. We will randomize *n* = 82 participants equally to 16 months of PDAE (*n* = 41) or to walking as aerobic exercise WALK (*n* = 41) in blocks of two to reduce variability within treatment conditions. Participants will be stratified by sex and Hoehn & Yahr (H&Y) staging (I, II, or III). The 16-month intervention period will consist of Training (3 months) and Maintenance (13 months) phases. In Training, participants will complete 20 biweekly 90-min sessions. In Maintenance, participants will complete 90-min weekly sessions. To evaluate SNc neurodegeneration over the observation period, we will image patients at study entry and 16-month follow-up using fMRI sequences. We will compare SNc volume and iron accumulation estimates in PDAE vs. WALK to assess whether PDAE is more neuroprotective.

Participants will be assessed at baseline, 3 months (immediately post-Training), and at 16 months (immediately post-Maintenance) for OFF-times, cognition, and neuroprotection, as evaluated in the SNc. At a standardized time of day, participants will be tested on all outcome measures at least 12 h after their last dose of antiparkinsonian medications. Furthermore, participants will keep an OFF-time diary to corroborate MDS-UPDRS-IV assessments. Participants will be ON medications during intervention. In addition to the primary motor and cognitive outcome measures, participants will be tested on secondary behavioral motor and cardiovascular and cognitive outcomes. Participants will undergo NM-MRI and fMRI scans at baseline and 3 and 16 months assessments to investigate mechanisms by which cognitive benefits have been obtained and replicated by PDAE and whether PDAE vs. WALK is neuroprotective, as exhibited by slowed rate of NM loss and iron accumulation and increased functional connectivity with spatial cognitive areas.

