## Participants

Informed consent will be obtained prior to randomization. To account for 25% attrition, we will recruit 102 participants with PD for this study. For group assignment, we will recruit PD patients (age ≥40, Hoehn & Yahr stage I–III) who report OFF-time, indicated by score ≥1 on UPDRS-IV item 4.3, i.e., time spent in the OFF-state. Their PD diagnosis (ICD-10 G20^*^) will be based on established criteria (64) and determined by a board-certified neurologist with training in movement disorders. Individuals must present asymmetric symptoms that include at least three of the cardinal signs of PD (rigidity, bradykinesia, tremor, postural instability) and must show clear symptomatic benefit from antiparkinsonian medications (65). Participants will be recruited from the Atlanta VA HCS Movement Disorders clinic and the Emory Movement Disorders clinic, as well as at local Parkinson-related support groups, educational meetings, and community events. We will also recruit via the Michael J. Fox Foundation FoxFinder web-based registry. Based on the ≈60% prevalence of reported OFF-times among participants in ongoing studies and our ability to recruit one in five contacted participants, we plan to initially contact 656 potential participants to reach the enrollment goal.

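### Recruiting 102 at 25% attrition leaves about 76 completers, not the 82 behind the stated power, and one section randomises only 82

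*Protocol article*

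**What the plan says.** Power and Sample Size for the Primary Outcome sets d = 0.7 for the MDS-UPDRS-IV total score, described as the value "which is 64% of the observed effect size in our pilot study or 79% of the estimated effect vs. walking". Holm's procedure covers the 3- and 16-month comparisons: "The alpha levels will be 0.025 and 0.05 for *p*-values in ascending order". The section reports the result as "giving us 81 and 88% power for the comparisons at alpha level of 0.025 and 0.05, respectively" and ties its sample size to 41 completers per group, 82 in total. It then adds: "We will assume 25% attrition and will therefore recruit 102 participants with PD".

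Three other places give a sample size:

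- Participants: "To account for 25% attrition, we will recruit 102 participants with PD for this study".
- Abstract: "We will randomly assign 102 individuals".
- Overall Study Design: "We will randomize *n* = 82 participants equally to 16 months of PDAE (*n* = 41", with the same number in the walking arm.

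So 82 is the number of completers in the power section and the number randomised in the design section. The number randomised is 102 in the Abstract and 82 in the design section.

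**The concern.** There are two separate faults.

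The first is the allowance for attrition. If a fraction of those recruited is lost, the required number of completers has to be divided by the fraction retained. The figure of 102 looks like the completer count multiplied by 1.25 instead. The article shows no formula, so this is an inference, but 82 x 1.25 = 102.5 fits closely. The result is a recruitment target that falls short of 82 completers under the plan's own attrition rate.

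The second is the number randomised. Randomisation comes before attrition, so 82 randomised and 82 completers cannot both be true when a quarter are expected to drop out. A reader cannot tell from the article whether the trial stops randomising at 82 or at 102.

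What is at stake is the power claim for the primary outcome at 16 months, the timepoint that carries the full attrition. Neither stated sample size yields the 41 completers per arm to which that claim belongs.

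**Working it through.** **Inputs, all from the protocol article**

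- d = 0.7, alphas 0.025 and 0.05, 41 completers per group, 25% attrition, 102 recruited: Power and Sample Size for the Primary Outcome.
- 82 randomised, 41 per arm: Overall Study Design.
- 102 randomised: Abstract.
- Sidedness is not stated. Two-sided is assumed because it reproduces both stated powers. One-sided tests at 41 per arm give 87.9% and 93.3%, which do not fit.

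**Step 1. Reproduce the stated power**

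Two-sample t-test with noncentrality d x sqrt(n/2) and 2n - 2 degrees of freedom. With n = 41, the noncentrality is 0.7 x sqrt(20.5) = 3.17 on 80 degrees of freedom. Power is 81.0% at alpha 0.025 and 87.9% at alpha 0.05. These are the article's 81% and 88%, so the stated power belongs to 41 analysed per arm.

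**Step 2. Check the recruitment figure**

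- Required: 82 / (1 - 0.25) = 109.3, rounded up to 110 (55 per arm).
- Stated: 102, close to 82 x 1.25 = 102.5.
- Completers from 102: 102 x 0.75 = 76.5, about 38 per arm.
- Attrition that 102 can absorb: 1 - 82/102 = 19.6%.

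**Step 3. Power for each reading of the sample size**

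Same t-test, d = 0.7, 25% lost:

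| Reading | Completers | Per arm | Power, alpha 0.025 | Power, alpha 0.05 |
|---|---|---|---|---|
| As powered | 82 | 41 | 81.0% | 87.9% |
| 102 randomised | 76.5 | 38 | 77.6% | 85.3% |
| 82 randomised | 61.5 | 31 and 30 | 66.8% | 76.7% |

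With 102 randomised the shortfall is 81.0 - 77.6 = 3.4 points and 87.9 - 85.3 = 2.6 points. With 82 randomised it is 81.0 - 66.8 = 14.2 points and 87.9 - 76.7 = 11.2 points.

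The normal approximation gives 82.3% and 88.7% at 41 per arm, and 79.1% and 86.2% at 38 per arm. The fall is similar, 3.2 and 2.5 points, from a slightly higher start.

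**The case against.** The strongest reply is that the completer t-test is not the planned analysis. The article specifies a mixed model, intent-to-treat, on all available data with multiple imputation, and enrolled patients are followed to study end. Participants who stop the intervention but are still assessed contribute, as do those with only a 3-month value. The effect size was also lowered from 0.89 to 0.7 partly because the pilot effect came from people who finished. These points bear on how large the loss is. They do not rescue the calculation: the article itself chose completers as its power basis, it reduced d and inflated N as two separate steps, and imputation does not replace 16-month outcomes that were never observed.

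A second reply is that the 3-month comparison may be unaffected. This stands. Attrition by timepoint is not given, and if no more than 19.6% are lost by month 3, 102 randomised leaves 82 and the stated power holds there.

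A third is that 82 in the design section is probably a mislabelled completer count, since three other places give 102. That is the likelier reading, and it makes the 67% and 77% figures conditional. The article does not settle it, though. The Participants section plans 656 initial contacts at about 60% OFF-time prevalence and one in five recruited. If those rates multiply, 656 x 0.6 x 0.2 = 78.7, nearer to 82 than to 102; if only the one-in-five rate applies, 656 / 5 = 131.

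Finally, with 102 randomised the loss is only about 3 points. That is true, and this half alone would not threaten the trial.

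**Conclusion.** The point holds. The recruitment figure does not follow from the stated attrition, and the number randomised is contradicted within the article.

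On the plan's own completer basis, 102 recruits at 25% attrition give about 78% and 85% power at 16 months rather than 81% and 88%, so the stricter Holm step falls below 80%. If 82 were the number actually randomised, power would be about 67% and 77%. The contradiction over the number randomised is the more serious half, because it decides which of these applies.

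These figures assume a two-sided test, d = 0.7, the full 25% lost by 16 months, and dropouts contributing nothing to that comparison. If dropouts contribute some information, the real loss is smaller. The arithmetic error and the contradiction do not depend on any of these assumptions.

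**What to change.** 1. Make the Abstract, Overall Study Design, Power and Sample Size, and Participants sections give one number randomised. Keeping 102 means 51 per arm; in Overall Study Design, replace 82 randomised with 102 and label 82 (41 per arm) as completers wherever it appears.
2. Then correct the link between 102 and the power claim in one of two ways: restate 16-month power as about 78% (alpha 0.025) and 85% (alpha 0.05) at 25% attrition, or say that 102 supports 82 completers only if attrition is at most 19.6%.
3. If both 82 completers and 25% attrition are to be kept, the target is 110 (55 per arm).
4. State that the power calculation is two-sided, if that is what was used.

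Items 1, 2 and 4 are wording only: no extra participants, and a stated power about 3 points lower if that option is taken. Item 3 costs 110 - 102 = 8 more participants.
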